##### 9.1.2.1.2 Plasma piperazine levels, full blood count, renal function and liver function

A few minutes after the last ECG is taken (i.e. 4-6 hours after the last dose of each course), a 2 ml venous blood sample will be obtained for piperazine and azithromycin drug levels to determine the relationship between drug level and magnitude of QTc prolongation. The sample will also be used to determine the impact of monthly dosing on full blood count, renal and hepatic function.

Furthermore, at delivery, maternal placental blood and cord blood sample will be used for the same drug levels to quantify drug exposure to placental parasites and the neonate, respectively.

### 9.1.3 Laboratory and nutritional assays

Some laboratory assays will be conducted at collaborating institutions in Australia, United States of America, Canada, United Kingdom, and Europe. A detailed description of the assays and analyses are provided in Appendix VII. Description of other clinical and laboratory methods.

## 9.2 DATA COLLECTION METHODS & STORAGE

### 9.2.1 Data management

#### 9.2.1.1 Methodologies for data collection / generation

A combination of paper-based and electronic record forms will be used. For the questionnaires that are administered in paper format, the study will utilise HP Teleform software to design the paper-based CRFs for semi-automated transcribing into an electronic database using scanning and Optical Character Recognition, intelligent document recognition and data validation using checksum algorithms, cross-field validation, and human verification of information against source documents. Once validated, the data will be transferred to the target database along with a PDF of the original image of the CRFs, such that there is an electronic copy of all paper-based documents. For the electronic-only data capture, such as home visits to administer drug adherence and bed net questionnaires, we will use tablets with integrated sim cards to transfer encrypted data to the ODK or similar servers where the electronic clinical data for the participants will be hosted.

#### 9.2.1.2 Data quality and standards

The quality of questionnaire data collection and data entry will be maximised through training of field staff in the standardised questionnaire administration methodology. Field staff will be trained in the methodology for collecting data and will be expected to demonstrate competence before conducting fieldwork. All electronic CRFs and data validations processes for data captured through Teleform will incorporate range and consistency checks.

#### 9.2.1.3 Managing, storing and curating data

Verified and validated data from all 3 countries will be stored via the cloud on a secure server at LSTM in Liverpool and/or KEMRI, Kisumu, Kenya. The PIs from each site will have access to their site data on the central server. Locally, data will be backed-up on a continuous basis on a secure off-site server and on encrypted standalone hard drives.

Once the data validation phase is completed by the central data manager, the database will be locked and transferred to a statistical programmer who will do further syntax driven consistency checks and syntax driven data cleaning (e.g. in Stata). The statistical programmer will have access to the PDF copies of the source data. He/she will then prepare the database for data analysis by the trial statistician by creating the final variables for data analysis, such as the creation of the composite endpoints. The final cleaned database will be available as SAS, STATA and in SPSS format, with embedded data dictionary.

#### 9.2.1.4 Metadata standards and data documentation

The full study protocol, supporting documents and the full anonymised research database will be made publicly available once the study findings have been published. The data manager and statistical programmer will produce a document summarising the methods used to generate the

data with a full description of all procedures, analyses, data capture tools, coding and description of variables. This document will be available alongside the research database.

#### **9.2.1.5 Data preservation strategy and standards**

The majority of data collected will be captured using scannable paper-based forms. The scanned PDF copies will be used for archiving, and the original paper questionnaires kept in a dedicated lockable data storage room in country and then destroyed after a minimum period subject to the prevailing laws in each country. The research data will be stored for the long-term in the original electronic format, in a unified large database and a public database that contains all research data other than participant identifiable data. The public database will be updated when needed if software becomes obsolete to achieve long-term preservation. The data will be preserved in this way for 10 years or longer if still being accessed at that stage.

### **9.3 STATISTICAL METHODS**

#### **9.3.1 General principles**

All statistical analyses will be described in detail in the Statistical Analysis Plan (SAP) and finalised and signed before unblinding the study. One interim analysis and/or one sample size re-estimation will be conducted as described in sections 7.6.1.2, page 37 and 10.1.3, page 45. The study is designed as a superiority trial, so all tests will be two-sided and  $P$ -values  $<0.05$  will be used to define statistical significance. Analysis will be done using SAS and Stata.

##### **9.3.1.1 Analyses populations**

Primary analyses will be based on ITT population and secondary supportive analyses will be done on the PP population. Safety analysis will be performed on the safety population.

1. Intention-to-treat (ITT) population: This population consists of all randomised subjects who have a valid outcome;
2. Per-protocol (PP) population: This population is a subset of the ITT population. Subjects with major protocol deviations will be excluded from PP population. Major protocol deviations will be defined in the SAP.
3. Safety population: This population is a subset of the ITT population, consisting of all randomised subjects who receive at least one dose or partial dose of study drug.

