### **7.3.5 Removal of participants from study**

#### **7.3.5.1 Removal of participants from therapy and/or assessment**

Participants can discontinue from the study for any one of the following reasons:

1. Screening error resulting in incorrect enrolment (found that subject did not meet required inclusion / exclusion criteria)
2. Withdrawal of consent at any stage or subject not willing to continue in the study
3. Suspected or confirmed allergic reaction to the study drug (removal from therapy only)
4. Safety reasons as judged by the investigator, study safety monitor or DMEC (removal from therapy only)

Where feasible, the participants who discontinue from the study treatment or from the study entirely will be asked about the reason(s) for their discontinuation and the presence of adverse events. Participants have the right to unconditionally withdraw from participation in the study without providing a reason. If a subject discontinues, data captured will contribute to the analysis up to the day prior to discontinuation, unless the subject indicates that she withdraws consent for any data captured up to that point. Every effort will be made to follow-up participants who discontinue due to drug related adverse events to determine the birth outcome. If a subject discontinues due to drug-related adverse events, all the assessments that would have been carried out at the next scheduled visit will be conducted at day 28 where reasonably possible (unless consent is withdrawn). This will be recorded in the CRFs. The study drug will be returned by the subject. Subjects that have discontinued the study prematurely will not be replaced.

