#### 7.5.5.3 *Unscheduled postnatal visits*

Women will be encouraged to attend the clinic if they or their baby become unwell during the follow-up postnatal period. Physical examinations and relevant blood samples will be conducted to guide management. Any illness will be treated as appropriate and according to standard local care. The date of attendance, diagnosis and treatment will be recorded on the CRF, and any adverse events reported according to standard procedures. Clinical care will also be provided for women who attend because of their own illness, but this will not be recorded as part of the study.

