#### 7.6.1.2 *Sample size for a standalone trial*

The sample size calculations for the standalone trial were conducted using PASS software. The total sample size will be 4,680 women (1,560 per arm) across three countries pooled. A sample size of 4,020 women (1,340 per arm) will achieve 80% power trial to detect a  $\geq 20\%$  reduction in the primary endpoint from 21.3% with IPTp-SP to 17.0% ( $RR=0.80$ ) ( $\alpha=0.05$ ) (90% power to detect a 23.0% reduction). 4,035 (1,345 per arm) women are required to allow for 1 interim analysis using the Lan-DeMets spending function with O'Brien-Fleming type boundaries to preserve the overall two-sided type I error rate for efficacy (see.10.1.3, page 45).

We will recruit 4,680 women (1,560 per arm) to allow for 13.7% loss to follow-up, which is approximately double the rate of loss to follow-up for this same primary composite endpoint in our recently completed MiP trials in Malawi (N=1873, across 2 arms) and Kenya (N=1546, across 3 arms). These trials involved similar sample sizes per country as in the proposed study, however the higher rate of loss to follow-up is used for our current sample size calculations since not all hospitals will have been part of the previous studies.

This same sample size of 1,340 completers per arm also provides 80% power to detect a further 22.8% reduction ( $RR=0.772$ ) from 17.0% in the IPTp-DP alone arm to 13.1% in the IPTp-DP+AZ arm ( $\alpha=0.05$ ) (or 90% power to detect a 26.1% reduction [ $RR=0.739$ ] from 17.0% to 12.6%). The 21.3% primary endpoint prevalence in the control arm is the observed mean prevalence in the IPTp-SP arms of our previous trials in the same sites in Kenya and Malawi, which also provided LLINs on enrolment, and in observational cohort studies in Tanzania.

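### Section 9.3.1.1 gives the safety population two conflicting definitions; read literally, one drops dosed women who have no ascertained outcome

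*Protocol*

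**What the plan says.** Protocol section 9.3.1.1 sets three analysis populations. Of the ITT population it says: "This population consists of all randomised subjects who have a valid outcome". What makes an outcome valid is not stated. Of the safety population it says: "This population is a subset of the ITT population, consisting of all randomised subjects who receive at least one dose or partial dose". The same section directs that "Safety analysis will be performed on the safety population".

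Two other places bear on this. Section 7.3.5.1, on removal from therapy or assessment, says: "If a subject discontinues, data captured will contribute to the analysis up to the day prior to discontinuation". The only exception is a woman who withdraws consent for the data already collected. Section 7.6.1.2 plans for missing outcomes: "We will recruit 4,680 women (1,560 per arm) to allow for 13.7% loss to follow-up".

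Safety is part of the primary objective in section 5.1, alongside superiority.

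**The concern.** A safety set should contain everyone exposed to study drug. Here membership also depends, through the nesting in ITT, on whether an outcome was later obtained. That is settled after randomisation and after dosing, so a woman could take study drug, have an event recorded, then be lost or withdraw, and be in no analysis population.

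Loss need not be unrelated to tolerability, and it could differ between arms. Table 2 shows a one-day SP course against three-day DP courses, with AZ or its placebo added at enrolment. Section 8.2.1 provides a placebo for AZ only, so women can tell SP from DP. For women who stop because of drug-related events, section 7.3.5.1 promises best efforts, but no guarantee, to obtain the birth outcome. Some safety and tolerance endpoints, such as vomiting after the first observed dose, arise long before any birth outcome, and there is no reason to make them conditional on one.

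**Working it through.** **Step 1: do the two clauses agree?** Let R be the randomised women, D those who took at least one full or partial dose, and V those with a valid outcome.

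- ITT = R and V.
- First clause of the safety definition: the safety set lies inside R and V.
- Second clause: the safety set is R and D.

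Both hold only if every woman in D is also in V, that is, if no dosed woman lacks a valid outcome.

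**Step 2: does the plan expect dosed women without an outcome?** The inputs are from section 7.6.1.2.

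The plan's own figures first. With 21.3% against 0.80 × 21.3% = 17.04%, two-sided alpha 0.05, 80% power and no continuity correction, the usual two-proportion formula is

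n = [1.960 × √(2p̄(1−p̄)) + 0.842 × √(p₁(1−p₁) + p₂(1−p₂))]² / (p₁−p₂)²

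with p̄ = 0.1917. It gives 1,340 per arm, as stated. For the interim analysis, "4,035 (1,345 per arm) women are required to allow for 1 interim analysis". Allowing for loss, 1,345 / (1 − 0.137) = 1,559, against 1,560 stated. The plan's figures are reproduced.

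Planned number without a primary outcome:

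- From the loss rate: 0.137 × 4,680 = 641; per arm 0.137 × 1,560 = 214.
- From the gap to the required number: 4,680 − 4,035 = 645; per arm 1,560 − 1,345 = 215. As a share, 645 / 4,680 = 13.8%.
- In the two DP arms together (3,120 women): 0.137 × 3,120 = 427, or 2 × 215 = 430.

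The 13.7% is a cautious allowance, described as "approximately double the rate of loss to follow-up for this same primary composite endpoint in our recently completed MiP trials". Half of it is 6.85%:

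- 0.0685 × 4,680 = 321; per arm 0.0685 × 1,560 = 107.

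These are upper bounds on the dosed women affected, because they assume that every woman without an outcome had taken study drug. Most would have: section 7.3.1.2.1 has day-0 doses directly observed. But section 7.3.2.1.1 withholds study drug at enrolment from febrile women with a positive rapid test, so a few could be lost undosed.

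**Step 3: does another section settle the conflict?** Section 7.3.5.1 lets data count up to the day before discontinuation and sets no condition on outcome. The nesting blocks this for any woman who discontinues and has no outcome. No section lifts the valid-outcome condition for safety.

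**Step 4: a separate, minor inconsistency in data capture.** Section 7.5.5.3 first says that attendance, diagnosis and treatment at unscheduled postnatal visits are recorded and that adverse events are reported. Of care for a woman's own illness it then says: "but this will not be recorded as part of the study". Table 1 schedules adverse event assessment at both postnatal visits, and section 7.4.2.2 lists serious and other adverse events as safety outcomes. These statements do not fit together.

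**The case against.** The strongest reply is that the second half of the sentence already gives the right definition, so this is a slip of wording and not a decision to exclude anyone. That stands in part: the exclusion is the literal effect of the subset clause, not a certain outcome. But an analyst cannot follow both halves, and the protocol does not say which prevails.

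It may also be said that an outcome could be judged valid endpoint by endpoint, so that a woman with any safety record counts. The text does not rule this out, but it does not say it either.

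A reader might infer more than the documents support, in five ways.

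- *Women who do not deliver under study are dropped.* Foetal loss is part of the primary outcome (7.4.1) and is assessed monthly, with tracing (9.1.1.2). Home deliveries are identified through community health workers (7.5.4). Only women with no ascertained outcome are affected.
- *Intolerant women are selectively removed.* This is possible but not shown. Section 7.3.5.1 makes allergy and safety stops removal from therapy only. Under 9.1.2.1.1, women with a confirmed QTc above 480 ms stay in the study.
- *Safety oversight is impaired.* Reporting under section 10.2.4 carries no outcome condition.
- *Maternal deaths to 42 days go unrecorded because of 7.5.5.3.* Section 9.1.2 records vital status at every scheduled and unscheduled visit, and 10.2.4 requires all serious adverse events to be reported.
- *ITT itself must be redefined.* Handling of missing outcomes can be left to the SAP, and repairing the safety set does not depend on it.

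**Conclusion.** The point holds as a contradiction in the definition of the safety population. The subset clause conflicts with the other half of its own sentence and with section 7.3.5.1 whenever a dosed woman has no valid outcome, and the sample size plans for such women. Leaving detail to the SAP does not cure this, because the protocol fixes the definition itself.

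Applied literally, the clause could take up to about 14% of randomised women out of the safety analysis at the planned loss, and about 7% at the past rate. This rests on two assumptions: that a valid outcome means the primary outcome, and that each woman without one had taken at least one dose. The clause could bias the safety comparison as well as shrink the set, but by how much and in which direction cannot be derived from the document. Since safety is part of the primary objective, the conflict should be settled before any safety analysis is run. The postnatal recording sentence is a separate, minor matter.

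**What to change.** In section 9.3.1.1, delete the clause that makes the safety population a subset of ITT. Define the safety population as all randomised women who received at least one full or partial dose of study drug, whatever their outcome status. Carry the same definition into the SAP. At the planned loss this restores up to 641 to 645 women, so that up to 4,680 are eligible instead of about 4,035 to 4,039. The cost is one sentence, with no change to the sample size or visits.

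Separately, reconcile the last sentence of section 7.5.5.3 with Table 1 and section 7.4.2.2, so that it is clear whether a mother's own illness at unscheduled postnatal visits is recorded. The cost is wording and, if it is to be recorded, one line on the case record form.

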#### **9.3.2 Assessment of efficacy**

##### **9.3.2.1 Primary endpoint analyses**

The generalised linear model (GLM) with the log-link function and binomial distribution (log-binomial regression) will be used to analyse the primary endpoint. The GLM model will have the treatment arm as the only predictor and country (Kenya, Malawi and Tanzania) and gravidity (pauci and multigravidae) as control variables, from which (unadjusted) risk ratio (RR) and its 95% confidence intervals (CI) of having a primary endpoint will be derived. Covariate-adjusted analyses for the primary endpoint will also be conducted by adding pre-specified covariates into the above unadjusted GLM analysis to derive the adjusted RR (95% CI). Imputation for baseline missing covariates will be made for covariate adjusted analysis.

In addition to the final analysis, the primary statistical hypothesis will be tested in an interim analysis when approximately 75% of women have enrolled as described in more detail in section 10.1.3, page 45.

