|                                               | 2. IPTp-DP: Dihydroartemisinin-piperaquine [3 to 5 tablets of DP (tablets of 40 mg of dihydroartemisinin and 320 mg of piperaquine, based on bodyweight) daily for 3 days] + placebo AZ                                                                                                    |                            |                                           |                    |
|                                               | 3. IPTp-SP: stat course of 3 tablets of quality-assured SP (tablets of 500 mg of sulphadoxine and 25 mg of pyrimethamine)                                                                                                                                                                  |                            |                                           |                    |
| Study type                                    | Interventional                                                                                                                                                                                                                                                                             |                            |                                           |                    |
|                                               | Allocation: randomised; intervention model: parallel assignment; arms: 3; allocation ratio: 1:1:1; stratified by site. Masking: Partially placebo controlled                                                                                                                               |                            |                                           |                    |
|                                               | Primary purpose: Treatment and prevention                                                                                                                                                                                                                                                  |                            |                                           |                    |

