**Hypotheses:**

- IPTp with DP is superior to IPTp with SP in preventing adverse pregnancy outcomes.
- The combination of DP with single 2 day course of AZ at first antenatal clinic visit further reduces adverse pregnancy outcomes compared to IPTp with DP alone.

**Overview Study Design:** An international, multi-centre, 3-arm, parallel, partially placebo-controlled, individually randomised, phase-3, superiority trial involving 4,680 (1,560 per arm) pregnant women in approximately 10 sites in areas of high malaria transmission and high SP resistance in western Kenya, northern-eastern Tanzania and southern Malawi. HIV-negative pregnant women (all gravidae) attending for antenatal care (ANC) between 16 and 28 weeks' gestation inclusive, assessed by ultrasound dating, will be eligible. Women will be seen monthly until delivery. Mothers and infants will be followed for 6 to 8 weeks post-partum. Permuted block randomisation, stratified by site and gravidity group, will be used. Allocation concealment will be ensured by using sequentially numbered, sealed, opaque envelopes.

The study will include nested cardiac safety monitoring in a sub group of women. Other components of evaluation of primary and secondary trial outcomes include molecular marker studies of antimalarial resistance, and antimicrobial activity of and resistance to azithromycin studies. We will also look at the impact on **TRANSPLACENTAL ANTIBODY TRANSFER AND MULTI-PATHOGEN NEONATAL CELL MEDIATED IMMUNE RESPONSES**, on maternal and neonatal nutritional outcomes, and at correlations between biomarkers of placental function and adverse birth outcomes.

*Sites:* The study will be conducted in approximately 10 sites in 3 countries, selected because they are situated in areas with high malaria transmission and high SP resistance.

*Study Population:* HIV-negative pregnant women (all gravidae) between 16 and 28 weeks' gestation, as assessed by ultrasound dating who have not yet started IPTp during the current pregnancy.

*Study Interventions:* 1. Standard 3-day course of DP (40/320mg) per day based on body weight (Eurartesim) given monthly, plus AZ, 2g as 2x500mg daily for 2 days at enrolment, followed by standard 3-day course of DP only, given monthly; 2. Standard 3-day course of DP (40/320mg) per day based on body weight (Eurartesim) given monthly, plus placebo AZ at enrolment; 3. Standard single-day stat course of quality-assured SP given monthly.

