*Outcome Measures:* Primary efficacy outcome: 'Adverse pregnancy outcome' defined as the composite of foetal loss (spontaneous abortion or stillbirth), or singleton live births born small-for-gestational age (SGA), or with low birthweight (LBW), or preterm (PT) (SGA-LBW-PT), or subsequent neonatal death by day 28.

*Follow-up procedures:* Enrolment at first antenatal visit and follow-up at routine scheduled antenatal care visits monthly with administration of intervention at all visits.

*Sample size:* 4,680 women (1,560 per arm) , allowing for 1 interim analysis

*Data Analysis:* Log-binomial regression will be used to analyse the primary endpoint, controlled for site and gravidity [paucigravidae (primi- and secundigravidae combined) and multigravidae].

*Partner institutions:* KEMRI and CDC Collaboration, Kisumu, western Kenya; College of Medicine, University of Malawi, Malawi; MLW Clinical Research Programme, Malawi; National Institute for Medical Research, Tanzania; Kilimanjaro Christian Medical Centre, Tanzania; Liverpool School of Tropical Medicine (LSTM); London School of Hygiene and Tropical Medicine (LSHTM); US Centers for Disease Control and Prevention (CDC); University of Copenhagen; Denmark University College London; University of Tampere, Finland; University of Bergen, Norway; University of Massachusetts, Worcester, USA; University of Melbourne, Melbourne, Australia; University of Toronto, Canada.

*Funding:* Joint Global Health Trials Scheme, Medical Research Council/Wellcome Trust/DFID, UK; and the European and Developing Countries Clinical Trials Partnership (EDCTP).

**SPONSOR:** Liverpool School of Tropical Medicine (LSTM); [name], [contact]; Email: [[contact]](mailto:[contact]).

| Table 1: Summary Table of Study Design and Schedule of Assessment     |                        |                                                                                                                                    |                                 |                                                       |                 |                 |                                       |                                 |                     |

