### 8.1 ALLOCATION

Permuted block randomisation, stratified by site and two gravidity groups (paucigravidae [1st and 2nd pregnancies] and multigravidae) will be used to generate randomisation lists. This will be done by a statistician at LSTM who is not involved in the study. The randomisation assignments will be put in sequentially numbered, sealed, opaque envelopes, which will be opened sequentially upon enrolment of a study participant in each site. Stratification by gravidity is essential to ensure balanced distribution among study arms as this is the most important known effect modifier of susceptibility to malaria infection and the corresponding impact on pregnancy outcomes.

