### 9.3.2.2 Secondary endpoints analyses

These will also be analysed using GLMs with the treatment arm as the single predictor and country (Kenya, Malawi and Tanzania) and gravidity (pauci and multigravidae) as control variables. The point estimate of the treatment effects with 95% CI will be derived via specification of a GLM model for each secondary outcome depending on its distribution. For a binary outcome such as the components of primary endpoint, similar analysis to the primary endpoint analysis will be performed and the treatment effects measured as RR will be generated. For a continuous outcome like birthweight, a Gaussian distribution will be assumed and identity link function will be used. Correspondingly the mean difference and its 95%CI between two arms will be calculated. For a count outcome such as the number of SAEs, Poisson distribution and log link function will be used, from which incidence rate ratio (IRR) and its 95% CI will be computed.

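### The summary's primary model adjusts for site, the randomisation stratum, but sections 9.3.2.1 and 9.3.2.2 adjust for country; state one model, preferably with site

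*Protocol*

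**What the plan says.** Section 8.1 sets out the allocation: "Permuted block randomisation, stratified by site and two gravidity groups". The long summary (2.3.4) agrees: "Permuted block randomisation, stratified by site and gravidity group, will be used". The registration table (2.3.1) names site alone: "allocation ratio: 1:1:1; stratified by site". On the number of strata, 2.3.4 says: "The study will be conducted in approximately 10 sites in 3 countries".

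Two descriptions of the primary model follow. The data-analysis paragraph of 2.3.4 reads: "Log-binomial regression will be used to analyse the primary endpoint, controlled for site and gravidity". Section 9.3.2.1 names the same log-binomial regression but takes "country (Kenya, Malawi and Tanzania) and gravidity (pauci and multigravidae) as control variables". Section 9.3.2.2 carries the second description over to the secondary endpoints: "These will also be analysed using GLMs with the treatment arm as the single predictor and country (Kenya, Malawi and Tanzania) and gravidity". No reason is given for moving from site to country. Otherwise, the statistical methods use site only as a subgroup variable, or to define site-level subgroup characteristics (9.3.2.3).

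**The concern.** Site with about 10 levels and country with 3 levels give different models, so whoever writes the SAP must depart from one of the two statements. The version in 2.3.4 follows the randomisation. The version in 9.3.2.1 keeps the gravidity stratum and the between-country part of the site stratum, but drops site within country.

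Stratified blocks balance the arms within each site. A model without site does not credit that balance in full: its standard error is somewhat too large if risk differs between sites of one country. The protocol expects sites to differ, since 9.3.2.3 treats transmission intensity and SP resistance as site characteristics. What is at stake is a little precision and a single clear statement of the primary model.

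**Working it through.** **1. The plan's own sample size.** Inputs from 7.6.1.2: 21.3% against RR 0.80, which is 0.213 × 0.80 = 0.1704 (printed as 17.0%); two-sided alpha 0.05; 80% power.

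n = [1.96 √(2p̄q̄) + 0.8416 √(p₁q₁ + p₂q₂)]² / (p₁ − p₂)²

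With p̄ = 0.1917, the bracket is 1.0911 + 0.4678 = 1.5589, and 1.5589² / 0.0426² gives 1,340 per arm, as stated. The rounded 17.0% gives 1,314. For losses, 1,345 / (1 − 0.137) = 1,559, against 1,560 stated. The formula has no stratum term, so the sample size does not depend on site or country.

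**2. Share of outcome variance due to site.** The protocol gives no between-site SD, so this is an assumed range around a risk of 19%. R² = SD² / (0.19 × 0.81) = SD² / 0.1539, and the standard error is too large by a factor 1/√(1 − R²).

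| Site SD (points) | R² | SE too large by |
|---|---|---|
| 3 | 0.0009/0.1539 = 0.006 | 0.3% |
| 5 | 0.0025/0.1539 = 0.016 | 0.8% |
| 8 | 0.0064/0.1539 = 0.042 | 2.1% |

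On this linear approximation these are upper bounds, because country already absorbs part of the site variation.

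**3. Size and power.** Let s be the assumed within-country SD between sites, with 1,345 per arm, 21.3% against 17.0%, and mean risk 0.1915.

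- Size = 2[1 − Φ(1.96/f)], with f = √{(0.1915 × 0.8085 − s²)/(0.1915 × 0.8085)}.
- SE used by the country model = √{(0.213 × 0.787 + 0.17 × 0.83)/1,345} = 0.01515.
- True SE = the same expression with 2s² taken off the numerator.
- Power, country model = Φ{(0.043 − 1.96 × 0.01515)/true SE}.
- Power, site model = Φ{0.043/true SE − 1.96}.

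| s (points) | True size, country model | Power, country | Power, site |
|---|---|---|---|
| 0 | 5.0% | 81.0% | 81.0% |
| 4 | 4.9% | 81.1% | 81.4% |
| 6 | 4.7% | 81.3% | 81.9% |
| 8 | 4.5% | 81.5% | 82.6% |
| 10 | 4.3% | 81.8% | 83.5% |

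The largest loss is 83.5 − 81.8 = 1.7 points.

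**4. Simulation.** Log-binomial fits with 10 sites, two arms of 1,340 and 1,500 runs per setting. At the largest site variation tried (SD 0.4 on the log-risk scale) and a true RR of 0.80, both models estimate 0.799. The mean SE of log RR is 0.0789 with country and 0.0770 with site, a ratio of 1.025, and power is 82.0% against 83.2%. The ratio is of the same order as step 2 but slightly above its 8-point entry, so that table should be read as an approximation. Under RR = 1, for log-risk SDs of 0, 0.2 and 0.4, the rejection rates are 3.5%, 4.9% and 5.1% (country) and 3.6%, 5.3% and 5.8% (site). With Monte Carlo error of about 0.6 points these are too noisy to measure the difference in size, but the country model never rejects more often.

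**5. Enrolment values.** For an assumed correlation ρ of 0.4 to 0.6 between enrolment and later values, adjustment removes ρ² = 16% to 36% of the variance. Put the other way, the unadjusted variance is ρ²/(1 − ρ²) = 0.16/0.84 = 19% to 0.36/0.64 = 56% larger than needed.

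**The case against.** Country can be defended. The number of sites is approximate, recruitment is competitive between sites within a country (7.7.3), and a log-binomial model with about 10 site levels is harder to fit than one with three country levels. The gain from site is small over the whole assumed range, and nothing in the country model is anti-conservative. All of this stands, and it limits the size of the point. It does not remove the contradiction: the protocol does not argue for country, and 2.3.4 says site.

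A reader might infer three stronger things that the documents do not support.

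- That the analysis ignores a whole design factor. It does not: gravidity and country are both in the model, and only site within country is missing.
- That the primary model can be picked once results are known. Section 9.3.1 has the SAP finalised and signed before unblinding. Section 8.2.1 keeps the statistician blinded while writing it, and releases allocation only after database lock and approval of the SAP by the monitoring committee. Section 10.1.3.2 requires the interim plan to be written into the SAP before the interim analysis starts.
- That the result is biased or the false-positive rate inflated. The calculations show neither.

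A fallback for non-convergence and the covariates for individual secondary outcomes are details that a SAP commonly supplies. Their absence from the protocol is not an error.

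**Conclusion.** The contradiction is real and can be verified from the text: site in 2.3.4, country in 9.3.2.1 and 9.3.2.2, with randomisation by site. Its consequence is minor. The RR is unaffected, the planned sample size is unaffected, and inference under the country model is slightly conservative. The size and power figures rest on an assumed within-country between-site SD of 0 to 10 percentage points; if sites within a country hardly differ, the loss is nil. The case for changing is that one primary model should be stated, and that the one matching the randomisation is at least as precise for almost no cost.

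The point on enrolment values is a secondary improvement. It concerns continuous outcomes only, and its size depends on the assumed correlation.

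**What to change.** In 9.3.2.1 and 9.3.2.2, replace country with site next to gravidity group, so that both sections match 8.1 and 2.3.4. Keep country for descriptive display. If the sponsor prefers country, give the reason and correct 2.3.4 instead.

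The cost is a change of wording and about 7 more parameters (9 site terms instead of 2 country terms) with 4,035 women expected to complete. The log-binomial fit becomes somewhat more likely not to converge, and the SAP can name a fallback for that.

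As a minor addition to 9.3.2.2, for continuous secondary outcomes also measured at enrolment, such as haemoglobin, maternal weight and mid-upper arm circumference, add the enrolment value to the model. These measurements are already in the schedule (Table 1), so no new data are needed.
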